## Abstract

**Background:**

Pressure ulcers (PrUs) are ischemic wounds in the skin and underlying tissues caused by long-standing pressure force over an external bone or cartilaginous surface. PrUs are an important challenge for the overall health system because can prolong patient hospitalization and reduce quality of life. Moreover, 95% of PrUs are avoidable, suggesting they are caused by poor quality care assistance. PrUs are also costly, increasing national costs. For example, they represent about 5% of overall annual health expenses in Spain. Stages I and II PrUs have a combined prevalence of 65%. According main clinical guidelines, stage II PrUs (PrU-IIs) are usually treated by applying special dressings (polyurethane or hydrocolloid). However, little scientific evidence regarding their efficacy has been identified in scientific literature. Our aim is to assess the comparative efficacy of adhesive polyurethane foam and hydrocolloid dressings in the treatment of PrU-IIs in terms of healed ulcer after 8 weeks of follow-up.

**Methods/design:**

This paper describes the development and evaluation protocol of a randomized clinical trial of two parallel treatment arms. A total of 820 patients with at least 1 PrU-II will be recruited from primary health care and home care centers. All patients will receive standardized healing procedures and preventive measures (e.g. positional changes and pressure-relieving support surfaces), following standardized procedures. The main outcome will be the percentage of wounds healed after 8 weeks. Secondary outcomes will include cost-effectiveness, as evaluated by cost per healed ulcer and cost per treated patient and safety evaluated by adverse events.

**Discussion:**

This trial will address the hypothesis that hydrocolloid dressings will heal at least 10% more stage II PrUs and be more cost-effective than polyurethane foam dressings after 8 weeks.

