### Aim and hypothesis

The main hypothesis of this study is that hydrocolloid dressings would heal at least 10% more stage II PrUs than polyurethane foam dressings over 8 weeks of follow-up in patients with PrU-II.

The aim of the proposed protocol is to compare the efficacy of adhesive polyurethane foam dressings and adhesive hydrocolloid dressings in the treatment of PrU-II. The primary objective will be to assess the percentage of wounds healed after 8 weeks.

Secondary objectives include assessments of:

improvements in the clinical efficacy of both dressings, as measured by ulcer area (cm [2]), exudates, type of tissue (PUSH Scale) and time to healing (epithelial tissue).

treatment efficacy, as measured by PrU-II resolutionwithin study time.

safety, as determined by adverse events (AE) attributed to both dressings.

direct costs of both dressings, as measured by cost per healed ulcer and cost per treated patient.

convenience of dressing use, as determined by adherence properties, management of the dressing, comfort, pain during the healing procedure, number of dressings used and perilesional skin state.

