### Sample size

Assuming that 30% of patients in the polyurethane arm will show healing of PrU-II at 8 weeks, an alpha risk of 5%, a beta risk of 20% with bilateral contrast and a loss to follow-up of 15%, 410 individuals will be required in each treatment arm to detect a ≥10% difference in healed ulcers [22,23].

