### Statistical analysis

#### Intention to treat analysis (ITT)

All statistical calculations will be based on ITT analysis, including all patients randomized, whether treated or not, and including all patients who have withdrawn prematurely. This approach reduces any bias that may occur when participants not receiving assigned treatments are excluded from analysis. All tests will be two-sided and α-values of 0.05 will be considered statistically significant.

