#### Comparative analysis

In a bivariate analysis, a χ^2^ test will be used to assess whether the percentage of healed PrU-IIs differs significantly in the two treatment arms. Mean changes in PrU size will be compared using Student’s t-tests for normal distributions or the Mann-Whitney U test against the usual null hypothesis (non-normal distributions): (initial area-final area)*100/initial area). In addition, 95% confidence intervals will be calculated to assess the clinical significance of treatment.

A logistic regression model adjusted for potential confounders will be performed when patients are not equally distributed in both treatment arms. Relative and absolute risk reduction and number needed to treat, defined as the estimated number of ulcers needed to be treated with the chosen dressing for one additional ulcer to be healed will be estimated, along with their corresponding 95% CIs.

Time to healing in the two treatment arms will be calculated by the Kaplan-Meier method and compared using the log-rank test. A Cox regression model of proportional risks will be used when the models require adjustment for any statistically significant baseline variable.

Finally, a partial economic evaluation will be performed, including direct costs such as number of dressings used per patient, additional dressings used, materials used, labor cost per cured ulcer and further treatment cost. The overall differences in mean costs and effects between treatments will be calculated using Student’s t-tests.

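### The hypothesis claims at least 10% more healing and better cost-effectiveness, but the stated tests address a difference of zero and compare costs and effects separately

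*Protocol article*

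**What the plan says.** **Hypothesis.** Aim and hypothesis, in the protocol article, gives the main hypothesis as "hydrocolloid dressings would heal at least 10% more stage II PrUs than polyurethane foam dressings over 8 weeks of follow-up". The abstract's Discussion repeats it and adds a second claim: "hydrocolloid dressings will heal at least 10% more stage II PrUs and be more cost-effective than polyurethane foam dressings after 8 weeks".

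**Sample size.** The Sample size section starts from "Assuming that 30% of patients in the polyurethane arm will show healing of PrU-II at 8 weeks" and concludes that "410 individuals will be required in each treatment arm to detect a ≥10% difference in healed ulcers", with 5% two-sided alpha, 80% power and 15% loss to follow-up.

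**Healing analysis.** The Intention to treat section says "All tests will be two-sided and α-values of 0.05 will be considered statistically significant". The Comparative analysis section uses a chi-square test of whether the percentage healed differs between arms. It also plans 95% confidence intervals for judging clinical significance, and absolute and relative risk reduction and number needed to treat, each with an interval.

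**Economic analysis.** The named outcomes are cost per healed ulcer and cost per treated patient. The evaluation is called partial. Its cost items include dressings per patient and "labor cost per cured ulcer and further treatment cost". On the comparison, the text says "The overall differences in mean costs and effects between treatments will be calculated using" Student's t-tests.

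**The concern.** The hypothesis sets a minimum size for the benefit; the test asks only whether the benefit differs from zero. These are different questions, and no sentence says how the result will be read against 10 points. A significant difference clearly below 10 points could later be presented either as supporting the main hypothesis or as failing it.

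The economic claim has a similar gap. Saying that one dressing is more cost-effective is a statement about cost and healing together. Two separate t-tests do not provide it, and average cost per healed ulcer in each arm does not show what an additional healed ulcer costs. The hard case is the one where one dressing both heals more and costs more, and there the stated method is silent.

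**Working it through.** **1. Reproduce the stated sample size.** Inputs from the Sample size section: p1 = 0.30, p2 = 0.40, two-sided alpha 0.05 (z = 1.960), power 80% (z = 0.842). With mean proportion 0.35:

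n = [1.960·√(2·0.35·0.65) + 0.842·√(0.30·0.70 + 0.40·0.60)]² / 0.10² = (1.322 + 0.565)² / 0.01 ≈ 356 per arm.

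356 × 1.15 = 409.4, which rounds up to the stated 410. (Dividing by 0.85 would give 419, within about 3%.) The 410 is therefore the size for a test of zero difference with 10 points as the alternative. With 15% lost, 410 × 0.85 = 348.5, or about 349 evaluable per arm.

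**2. Smallest significant observed difference, control arm at 30%.** Find d such that d / √(2·p̄(1−p̄)/m) = 1.96, where p̄ = 0.30 + d/2.
- m = 410: d ≈ 0.0645 (standard error 0.0329), about 6.5 points, 95% CI about 0.0 to 12.9.
- m = 349: d ≈ 0.070 (standard error 0.0357), about 7.0 points, 95% CI about 0.0 to 14.0.

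**3. Chance of significance when the true gain is below 10 points.**
- True 5 points: 29% (m = 349) to 33% (m = 410).
- True 7 points: 50% to 57%.

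**4. Chance that the lower 95% limit exceeds 10 points.** P = 1 − Φ(1.96 − (Δ − 0.10)/SE), with SE = √[(0.30·0.70 + p2(1−p2))/m] and p2 = 0.30 + Δ. The values of Δ above 10 points are assumptions.

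| True difference Δ | m = 349 | m = 410 |
|---|---|---|
| 10 points | 2.5% | 2.5% |
| 15 points | 28% | 32% |
| 20 points | 79% | 85% |

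The observed difference needed for a lower limit above 10 is about 17.1 points (m = 349) or 16.6 points (m = 410).

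**5. Cost-effectiveness.** The documents give no cost means, standard deviations or value placed on a healed ulcer, so no cost figure can be computed. The structure can be checked. Let ΔC be the difference in mean cost per patient and ΔE the difference in proportion healed.
- ΔC ≤ 0 and ΔE ≥ 0, at least one strictly: the better arm is clear without a joint measure, apart from the joint uncertainty.
- ΔC > 0 and ΔE > 0: the answer depends on ΔC/ΔE, or on net benefit. Neither t-test yields it, and the two average ratios do not either.

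The uncertainty also matters. At an observed ΔE of 0.10 with 349 per arm, SE = 0.0359 and the 95% CI is 0.10 ± 1.96 × 0.0359 = 0.030 to 0.170. Even with ΔC held fixed, ΔC/ΔE would run from about 6·ΔC (1/0.170) to about 34·ΔC (1/0.030). Separate tests do not carry this through to the cost-effectiveness conclusion.

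**The case against.** **The design and the primary test agree.** The sample size is for a two-sided test of zero difference, and that test is planned. Putting the design difference into the research hypothesis is common loose wording, and correcting it changes neither the test nor the sample size. This stands, and it places the healing fault in the hypothesis wording. The 2.5% is not the power of a planned analysis; it shows what the present wording would demand.

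**A safeguard exists.** Confidence intervals, including one for the absolute difference, are planned for judging clinical significance. A reader might infer that the trial will announce at least 10% more on the strength of p < 0.05; no passage says so. What is missing is only a rule tying the interval to 10 points.

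**A relative reading of 10%.** A reader might infer that the benefit could mean 30% against 33%. The Sample size section rules this out: 410 per arm reproduces for 30% against 40%, whereas 30% against 33% would need several thousand per arm.

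**Labour cost.** A reader might infer from the phrase about labour per cured ulcer that nursing time on unhealed ulcers is dropped. The documents do not support that. The secondary outcomes require nurse time in both arms, and the Work plan records it at baseline, at visits 2 to 7 and at dressing changes between visits, without restriction to ulcers that heal. The more natural meaning is total labour divided by ulcers healed. The phrase needs clarifying, since it stands beside per-patient items.

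**The economic part is secondary, partial and open to later detail.** It is absent from the main hypothesis in the body text, and an article may leave technical detail to another document. But the article does fix a method, separate t-tests, and its abstract makes a comparative claim which that method cannot settle. This part of the point therefore survives.

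**Conclusion.** The point holds as a mismatch between the hypothesis as worded and the analyses as stated. Followed exactly, the significance test cannot establish at least 10 points more healing, since it can be positive from about 6.5 to 7.0 points observed. The planned confidence interval could establish it, but no rule says so, and at a true difference of 10 points it would succeed only 2.5% of the time. The separate t-tests cannot establish better cost-effectiveness when costs and effects point in opposite directions for the decision.

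The figures assume 30% healing on polyurethane, normal approximations, and between 349 and 410 analysed per arm. They do not show an error in the sample size or in the choice of a two-sided test of zero difference. The correction is worth making before results are known, but it does not threaten the trial's ability to estimate the difference in healing.

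**What to change.** 1. In the abstract and in Aim and hypothesis, state the primary hypothesis as a two-sided test of no difference in the proportion healed at 8 weeks, with 10 percentage points named as the design difference.
2. In the Comparative analysis section, state that a benefit of at least 10 percentage points will be claimed only if the lower limit of the already planned 95% CI for the absolute difference reaches 10.
3. Replace the separate t-tests of costs and effects with the incremental cost per additional healed ulcer, or net benefit, with a patient-level bootstrap interval. Count all costs, labour included, per randomised patient. Keep average cost per healed ulcer as descriptive. Alternatively, drop the claim of better cost-effectiveness from the abstract.
4. Clarify that the labour item covers nursing time on all study ulcers, healed or not.

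The cost is a more modest claim, some rewording and a little more analysis. The data needed are already to be collected, and the sample size does not change.

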**Trial registration:**

This trial has been registered with controlled-trials number ISCRCTN57842461 and EudraCT 2012-003945-14.

## Background

Pressure ulcers (PrUs) are ischemic wounds in the skin and underlying tissues, caused by continuous pressure from friction or shearing between an external surface and a bone or cartilaginous surface. Long-standing pressure can reduce capillary blood flow and lead to cell death, necrosis and broken tissue, or to additional serious complications, including osteomyelitis, sepsis, contractures, atrophy and psychological disorders [1,2]. These complications may delay mobilization and active rehabilitation, as well as reducing the ability of patients to live active and independent lives. PrUs can affect patients in all health care settings, provoke pain and discomfort, decrease quality of life and even increase morbidity and residence time in healthcare institutions [3,4].

PrUs can also increase direct and indirect healthcare costs and provide a negative image of healthcare institutions, attributable to deficits in the quality of care, especially since 95% of PrUs are preventable [1,2]. A national study has estimated that expenditures related to the onset of PrU amounts to approximately 5% of the annual healthcare spending in Spain [3,4].

A national prevalence study in 2006 by the GNEAUPP (Spanish acronym of National Group for the Study and Advice in Pressure Ulcers and Chronic Wounds) showed a wide variability in PrUs prevalence among types of institutions. PrUs have been reported to occur in 3.73% of patients in domiciliary care, 8.24% of hospitalized patients and 6.1% of patients in nursing homes. Moreover, 2.1% of patients with PrUs were aged 0 to 45 years, 6.4% were aged 46 to 64 years and 87.4% were aged ≥ 65 years [5]. Within each category, PrU incidence was very variable, ranging from 3-29% in hospitalized patients. Moreover, PrUs have been observed in 66% of elderly individuals (risk population) with femur fractures [4-7].

The European Pressure Ulcer Advisory Panel (EPUAP) has classified PrUs in four stages. Stages I and II are more frequent, with a combined rate of about 65% [5], although it differs among studies [8-15]. The EPUAP has defined stage II PrU (PrU-II) as involving a partial loss in skin thickness, affecting the epidermis and/or dermis. These are considered superficial ulcers, clinically manifesting as abrasions or blisters [8,16].

Prevention is the best treatment for PrU. However, despite Good Clinical Practice Guidelines (GCP), [17-20] which report the effectiveness of preventive activities (adequate nutrition, effective pressure relief, positional changes, management of incontinence and elimination of shearing and friction forces), there is little scientific evidence supporting the efficacy of these measures in avoiding further problems related to PrUs [1-3].

In contrast, evidence has suggested that PrUs healing in a moist environment, using special or modern dressings, is more cost effective than traditional cure or dry-to-wet dressings (i.e. dressings that do not maintain a moist environment) because the former stimulate cell proliferation. In addition, special dressings act as a barrier against bacteria, absorb excess wound fluid, reduce pain during the healing process and create the right conditions (moist environment) for healing or scarring [1,3,18-20].

The benefits of a moist environment have led to the development of a flowering variety of synthetic dressings (special or also called modern dressings). Use of these dressings depends on the availability of resources, PrU stage and morphology, and the presence of infection and/or necrosis [1,3,18-20].

Although GCP guidelines indicate that the special dressings most frequently used to treat PrU-II are hydrocolloid and polyurethane foam dressings. To date, however, systematic reviews and clinical trials have established a poorly and scarcely evidence of their effectiveness. Although studies have shown benefits of polyurethane dressings, their benefits did not differ significantly from those of hydrocolloid dressings. In addition, these studies involved patients with various wound types (pressure ulcers and venous ulcers) and different PrU stages, which may have affected the results [1,3,18-21].

To overcome these limitations, the present study will compare two types of dressings in the treatment of PrU-IIs, both which are recommended and are part of habitual clinical practice [1,3,19,20]. However, due to the wide variability in both types of dressing, this study will compare the adhesive versions of polyurethane and hydrocolloid dressings.

### Aim and hypothesis

The main hypothesis of this study is that hydrocolloid dressings would heal at least 10% more stage II PrUs than polyurethane foam dressings over 8 weeks of follow-up in patients with PrU-II.

The aim of the proposed protocol is to compare the efficacy of adhesive polyurethane foam dressings and adhesive hydrocolloid dressings in the treatment of PrU-II. The primary objective will be to assess the percentage of wounds healed after 8 weeks.

Secondary objectives include assessments of:

improvements in the clinical efficacy of both dressings, as measured by ulcer area (cm [2]), exudates, type of tissue (PUSH Scale) and time to healing (epithelial tissue).

treatment efficacy, as measured by PrU-II resolutionwithin study time.

safety, as determined by adverse events (AE) attributed to both dressings.

direct costs of both dressings, as measured by cost per healed ulcer and cost per treated patient.

convenience of dressing use, as determined by adherence properties, management of the dressing, comfort, pain during the healing procedure, number of dressings used and perilesional skin state.

## Methods and design

### Study design

This will be a multicenter, randomized trial evaluating and comparing the efficacy of the adhesive polyurethane foam and hydrocolloid dressings in patients with PrU-II within the context of habitual prevention measures.

### Setting and eligibility criteria

This study will recruit patients who receive primary health assistance, including patients able to attend the primary health center or receive health assistance in homes, nursing-homes and non-acute long term hospitalization centers. Each patient must present with at least one PrU-II.

#### Inclusion criteria

Age ≥ 18 years.

Confirmed diagnosis of PrU-II. If a patient has more than one PrU-II, only the largest diameter ulcer will be assessed. Other PrU-II will receive the best treatment elected by the study nurse.

#### Exclusion criteria

Stage I, III or IV PrU only.

Non classifiable PrU.

Surgical treatment prior to PrU and/or PrU in previously irradiated areas.

Participation in another clinical trial within 3 months of study entry.

Allergy or hypersensitivity to materials in the study dressings.

Signs of PrU basal infection (sepsis/bacterial), cellulitis or osteomyelitis. Patients successfully treated for infection can be included if the PrU can be classified as stage II.

Venous ulcers and/or diabetic feet.

Type I diabetes.

Situations of extreme severity and/or agony; e.g. patients in terminal phase with <3 points on the Braden scale and/or a life expectancy < 1 month.

### Recruitment

Each primary health center or nursing home will have one or two study nurses to assess eligibility criteria, to invite potential candidates to participate in the clinical trial and to carry out all protocol procedures (see section on Interventions).

Potentially eligible patients will be recorded, as well as reasons for exclusion. All included patients will be given a patient information sheet and an informed consent form. Signing of the latter is essential for study inclusion.

If a patient’s clinical condition makes signing of the informed consent form impossible, a relative or guardian will be responsible for signing; however, those patients must clearly indicate orally their willingness to participate in the study.

Any included patient who drops out or is lost during the clinical trial process will be recorded on the appropriate form.

### Randomization

Participants will be enrolled consecutively by their study nurse. Each participating center will have a unique randomization list. This sequential randomization will be generated in blocks of 12, up to a maximum of 24 recruited patients per center (see Additional file 1: Figure S1).

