### Blinding

Due to an inability to mask the appearance of the two dressings, it will only be possible to mask the final evaluation of PrU.

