### Work plan

Before the trial begins, the study protocol will be presented to all research team members in a special meeting. A training session lasting 3–4 h will include a review of the inclusion and exclusion criteria, provide instructions regarding interventions and the procedure to use to fill out the Case Report Form (CRD), as well as assessing the ethical requirements for the trial. The protocol to be used to collect information from each patient at each study visit will include (see Additional file 2: Table S1):

•**Selection visit (screening)**

Assessment of inclusion/exclusion criteria

Signing informed consent form

•**Visit 1 (baseline).***If patients agree to participate in the study at the selection visit, all scheduled activities for visit 1 can be performed at the selection visit. If patients require time to think about participating, these scheduled activities will be performed at visit 1.*

Randomization process

Collection of demographic data, including date of birth, sex, and place of usual care

Risk factors for PrU, using the Braden scale

PUSH Scale registry, including area of each lesion (width × length), volume of exudates and tissue type

PrU photographic registry

Healing process registry: reason to change dressing, time treated by the nurse, materials used

Training about transverse care (positional changing and pressure reduction)

Recording of concomitant medications

Recording of adverse events

•**From Visit 2 to Visit 7 (Follow-up)**

Assessment of inclusion/exclusion criteria

Assessment of transverse interventions, from each patient’s diary and nursing files

PUSH Scale registry, including area of each lesion (width × length), volume of exudates and tissue type

Healing process registry: reason to change dressing, time treated by the nurse, materials used

Recording of concomitant medications

Recording of adverse events

•**Between visits.***The study protocol includes 8 study visits. If patients require a change of dressing, between visits,it must be recorded in the CRF, with the following information collected.*

Date of dressing change

Reason for dressing change (exudates, lack of adherence, other reasons)

Time treated by the nurse (mm:ss)

Materials used

•**Visit 8 or End of study**

PUSH Scale registry: diameter of each lesion (width × length), volume of exudates and tissue type.

Completion of the dressing scale comfort instrument by patients and study nurses

Braden scale

PrU photographic registry

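### A single disclosed block size of 12 on per-centre lists, with visible dressings, lets the enrolling nurse know up to about 1 in 7 allocations in advance

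*Protocol article*

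**What the plan says.** All references are to the protocol article.

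- **Randomization:** the study nurse enrols patients one after another, and every centre works from its own list. On how that list is built, the section says: "This sequential randomization will be generated in blocks of 12, up to a maximum of 24 recruited patients per center". No other block size is mentioned, and the cap of 24 is exactly two blocks.
- **Recruitment:** each centre has "one or two study nurses to assess eligibility criteria, to invite potential candidates to participate in the clinical trial", and the same nurses carry out all the trial procedures. Potentially eligible patients and the reasons for exclusion are logged.
- **Blinding:** "Due to an inability to mask the appearance of the two dressings", only the final evaluation of the ulcer is masked.
- **Main outcome variables:** a panel blinded to treatment judges healing from photographs.
- **Work plan:** the protocol is explained to the whole research team before the trial begins. Under Visit 1 the first item is "Randomization process"; the Braden scale, PUSH and the baseline photograph come further down the same list.

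**The concern.** Selection bias needs three things: someone who decides who enters, sight of earlier allocations, and a rule that links them to the next one. All three are in the text. The nurse assesses eligibility and invites, the dressings show which arm each earlier patient received, and a known block of 12 must end in balance. Once six patients in a block have had one dressing, every remaining place in that block is known.

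A nurse with a view on which dressing works better could then invite a patient with a promising ulcer, or delay one with a poor ulcer, according to the arm that is due. The arms would differ in prognosis at entry. Masked assessment of the outcome cannot undo that, and the adjusted logistic regression in the Statistical analysis section can correct only for baseline variables that were measured.

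**Working it through.** The protocol gives no predictability figure, so there is none to reproduce.

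**Inputs.** Block size 12 and a per-centre list capped at 24 (Randomization); 410 per arm, 820 in total (Sample size, Abstract). Equal arms imply 6:6 blocks, which is an assumption. The nurse is assumed to know the block size, and the nurses of one centre to share sight of past allocations.

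**Step 1: allocations certain in advance.** In a permuted block of 2m with m per arm, the expected number of certain places is 2m/(m+1). With m = 6 this is 12/7 = 1.71 per block, and 1.71/12 = 14.3%. Over 820 patients: 820/7 = 117.

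**Step 2: where they fall.** The chance that the next place is certain, by hypergeometric enumeration:

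| Place in block | 7 | 8 | 9 | 10 | 11 | 12 |
|---|---|---|---|---|---|---|
| Certain | 0.2% | 1.5% | 6.1% | 18.2% | 45.5% | 100% |

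Places 1 to 6 are never certain. The last three places hold (0.182 + 0.455 + 1)/1.71 = 95% of the certainty. At a full centre, patients 12 and 24 are always known.

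**Step 3: correct guesses.** Guessing the arm that is behind is right m + (4^m/C(2m,m) − 1)/2 times per block. With m = 6: 6 + (4096/924 − 1)/2 = 7.72 of 12, or 64.3%, against 50% by chance.

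**Step 4: dependence on filling the blocks.** Summing the table, a centre that stops at 9 patients has 0.078/9 = 0.9% certain allocations, and one that stops at 10 has 0.260/10 = 2.6%. One that stops at 18 has 1.71/18 = 9.5%, because the first six places of the second block add nothing. Only centres that stop at 12 or 24 reach 14.3%.

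**Step 5: possible bias (illustration, not a forecast).** Suppose every nurse favours the same dressing and exploits the pattern fully, and that the steered good- and poor-prognosis ulcers differ by d in healing. The protocol gives no d; 10 to 20 points is assumed.

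- Steering only on certain places shifts the arm difference by 0.143 × d = 1.4 to 2.9 points.
- Steering on every best guess shifts it by (0.643 − 0.357) × d = 2.9 to 5.7 points.

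The target difference is 10 points. With 30% healing in both arms and 410 per arm, the standard error is √(2 × 0.3 × 0.7/410) = 3.2 points. A two-sided 5% test with no true effect would then reject about 7% to 15% of the time in the first case and about 15% to 43% in the second.

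**Step 6: other block schemes.** For fixed blocks the certain share is 33% for size 4, 25% for 6 and 20% for 8. By simulation of 24 patients per centre, guessing the lagging arm is right 64.3% of the time for fixed 12, 67.3% for a random mix of 4/6/8, 65.3% for 4/6/8/10/12, and about 62.9% for 8/12/16.

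**The case against.** The strongest defence is that the design already contains safeguards and that 12 is a fairly large block. Enrolment is consecutive, so steering means passing over an eligible patient against a stated rule, and the log should show it. The primary outcome is judged by a blinded panel. Smaller fixed blocks would be worse, and the 14.3% holds only if blocks fill and the size is known; the article gives a cap per centre, not expected recruitment.

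Most of this stands as a limit on size. It does not remove the fault. The nurse who could steer also judges eligibility and keeps the log. The panel limits detection bias in the primary outcome, not unequal prognosis at entry.

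A reader might infer more than the text supports:

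- **That the list is not concealed.** The article refers to an additional file that is not shown, and an article may leave the release mechanism to the full protocol. The point here does not need that inference, because past allocations reveal the end of a known block under any concealment.
- **That the unblinded nurse sets the baseline for percentage area change.** Under Secondary outcome variables, members of the expert panel measure area from photographs with image software. The nurse takes the photograph and records width and length for PUSH.
- **That the study ulcer is chosen after allocation.** The rule to assess the largest ulcer is an inclusion criterion, and those criteria are assessed at the selection visit.
- **That baseline is recorded after allocation.** Randomization heads the Visit 1 list, but the list is not said to be a sequence.

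**Conclusion.** The point holds in limited form. One disclosed block size, per-centre lists, visible dressings and the same one or two nurses recruiting and treating make up to about 1 in 7 allocations certain in advance. The count of 117 out of 820 is a ceiling, not an expectation: it rests on 6:6 blocks that all fill, a known block size and shared sight of past allocations. The 64.3% rate of correct guesses rests on the same conditions.

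That is enough to permit selection bias at enrolment, but it does not show that bias will occur. The change should be made because it is cheap and because bias from unmeasured prognosis cannot be reliably repaired in the analysis. On Visit 1, the text only leaves the order open; it does not state a wrong one.

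**What to change.** 1. Vary the block size at random and avoid small blocks, for example a mix of 8, 12 and 16. This removes most certain knowledge of the next place and brings the guess rate to about 62.9%. A mix of 4, 6 and 8 would raise it to 67.3%, so varying the size is not enough by itself.
2. Keep the sizes out of the protocol text, training material and other documents that sites see. Outside release of allocations would not by itself stop inference from past ones.
3. State in Visit 1 that eligibility, consent, the study ulcer, Braden, PUSH and the baseline photograph are recorded before the allocation is released.

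The cost is a new list and a few lines of text. Balance within a centre becomes slightly less exact: the largest possible imbalance rises from 12/2 = 6 to 16/2 = 8, and a centre that reaches 24 is no longer certain to split 12:12. Stating the Visit 1 order costs next to nothing.
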